#### Anthropometry

Before the CPET, body weight and height are measured of participants wearing light clothes and no shoes. To measure body weight, we use a calibrated analogue balance and digital balance, depending on study center. Analogue values are rounded to the nearest 0.5 kg. Height is measured using a wall mounted tape measure, with values rounded to the nearest 0.5 cm. The same balance and tape measure are always used for all measurements of an individual participant. Body Mass Index (BMI) is calculated as weight in kilograms divided by height in meters squared (kg∙m^−2^). Waist and hip circumference (to the nearest 0.5 cm) are measured standing at the midway between lower ribs and iliac crest, and as the largest circumference between waist and thigh, respectively. Measurements are taken in duplicate and averaged.

#### Blood collection

Serum, plasma and cell pellet are derived from whole blood samples, processed within 4 hours and stored at -80 °C in the biobank of the University Medical Center Utrecht to be used for future analyses of biomarkers.

#### Adherence

Adherence incorporates both attendance at the supervised exercise sessions and compliance (i.e., performing the exercises according to exercise protocol). To monitor attendance, the physiotherapist documents presence of each participant at each session in a case report form. Furthermore, to monitor compliance, achieved heart rates and duration for the aerobic exercise components are documented, and weight and number of repetitions performed for the resistance components. In case of missed exercise sessions or non-compliance to the protocol, reasons are documented. At least every 4 weeks, this documentation is sent to the researchers for monitoring. Moreover, each physiotherapist is visited at least once by a member of the PERFECT study team, to ensure proper performance of the exercise protocol.

#### Recurrence and survival

Information on cancer recurrence, new primary tumors and (all-cause) death is retrieved from medical records and the Dutch Cancer Registry.

### Safety

CPET with electrocardiography is performed for exercise clearance before start of the exercise training. Adverse events reported by the patient or observed by physiotherapists, oncology nurses or physicians are recorded and serious adverse events are reported to the medical ethical committee. Malnutrition, dysphagia and weight loss are common problems in esophageal cancer patients [7], hence weight loss is not a goal of the exercise program. Body weight is therefore closely monitored by weekly supervised weighing by the physiotherapist. All physiotherapists are instructed to contact the researchers if weight loss exceeds 5% in 1 month, or 10% in total, upon which the study team will consult a dietitian or medical specialist.

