**Methods:**

The Physical ExeRcise Following Esophageal Cancer Treatment (PERFECT) study is a multicenter randomized controlled trial including 150 esophageal cancer patients after surgery with curative intent. Patients are randomly allocated to an exercise group or usual care group. The exercise group participates in a 12-week combined aerobic and resistance exercise program, supervised by a physiotherapist near the patient’s home-address. In addition, participants in the exercise group are requested to be physically active for at least 30 min per day, every day of the week. Participants allocated to the usual care group are asked to maintain their habitual physical activity pattern. The primary outcome is health-related quality of life (EORTC-QLQ-C30). Secondary outcomes include esophageal cancer specific quality of life, fatigue, anxiety and depression, sleep quality, work-related factors, cardiorespiratory fitness (VO_2peak_), muscle strength, physical activity, malnutrition risk, anthropometry, blood markers, recurrence of disease and survival. All questionnaire outcomes, diaries and accelerometers are assessed at baseline, post-intervention (12 weeks post-baseline) and 24 weeks post-baseline. Physical fitness, anthropometry and blood markers are assessed at baseline and post-intervention. In addition, adherence and safety are monitored throughout the exercise program.

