### Intervention

The standardized physical exercise program combines aerobic and resistance training and takes place twice weekly during 12 weeks. The individual components of the exercise program are described below in the sections ‘Aerobic training’ and ‘Resistance training’. All exercise sessions are supervised and guided by a physiotherapist, preferably an oncology physiotherapist. Since esophageal cancer care is centralized in the Netherlands, training at the treating hospitals might not be feasible for some patients due to relatively long travel distances. Before start of the PERFECT study, we interviewed 4 esophageal cancer patients, who all indicated a maximal travel distance between 5 and 15 km as acceptable. Therefore, the exercise program is offered close to home, either in a general physiotherapist practice or in a hospital nearby the patient’s home address. Each physiotherapist is trained by the PERFECT study team to perform the exercise sessions in a standardized way.

Although there is not yet enough evidence to draw definite conclusions about the most effective design of exercise programs [14], programs with moderate-to-vigorous intensity have been shown to have significant beneficial effects on HRQoL, whereas programs with mild-to-moderate intensity had not [11, 15]. With regard to the mode of physical activity, the ACSM guidelines on exercise for cancer survivors have included both aerobic exercise and resistance exercise [16, 17]. Therefore, we study the effectiveness of a moderate-to-vigorous intensity program, combining both aerobic and resistance exercise.

The exercise protocol has previously been shown to be safe and feasible in healthy overweight, postmenopausal women [18]. Exercise protocols with comparable content and intensity have been shown to be safe and feasible in patients with breast, colon, ovarian, cervix or testis cancer, or lymphomas [15, 19, 20]. The duration of every exercise session is 1 hour and includes a warming up (5 min), aerobic and resistance training (50 min) and a cooling down (5 min). In case of physical limitations, an adapted exercise program will be provided.

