### Study outcomes

Table 2 summarizes the outcomes measured in the PERFECT study. All questionnaire outcomes, diaries and the accelerometers are assessed at baseline, post-intervention (12 weeks post-baseline) and 24 weeks post-baseline. At baseline and post-intervention these outcomes are assessed during a study center visit. At 24-weeks participants receive the questionnaires by mail. Physical fitness and blood markers are assessed at baseline and post-intervention. Recurrence and survival will be assessed 2- and 5-year post-diagnosis. Socio-demographic data (age, sex, education, marital status) and smoking status are assessed at baseline with a self-developed questionnaire. Medical data (diagnosis, tumor type, disease stage, type of treatment, and comorbidities) are retrieved from medical records. Personal data are coded and all data are handled by the researchers in compliance with the Dutch Personal Data Protection Act. The PERFECT study is checked on safety for participants and validity of data by an independent monitor.

**Table 2 Tab2:** Study outcomes

Outcomes	Instrument	Baseline	12-week	24-week
Primary outcome				
Quality of life	EORTC-QLQ-C30	X	X	X
Secondary outcomes				
Esophageal cancer specific symptoms	EORTC-QLQ-OG25	X	X	X
Fatigue	Multidimensional Fatigue Inventory (MFI)	X	X	X
Anxiety and depression	Hospital Anxiety and Depression Scale (HADS)	X	X	X
Sleep quality	Pittsburgh Sleep Quality Index (PSQI)	X	X	X
Work-related factors	iMTA Productivity Cost Questionnaire (iPCQ)	X	X	X
Cardiorespiratory fitness	Cardiopulmonary exercise testing (CPET)	X	X	
Muscle strength	MicroFET handheld dynamometer	X	X	
Physical activity	Short questionnaire to assess health enhancing physical activity (SQUASH)	X	X	X
	ActiGraph accelerometer	X	X	X
	Exercise log		X	
Malnutrition risk	Patient-Generated Subjective Global Assessment Short Form (PG-SGA SF)	X	X	X
Dietary intake	3-Day food diary	X	X	X
Anthropometry	Body weight, height, BMI, waist and hip circumference	X	X	
Blood parameters	Serum, plasma and cell pellet	X	X	
Adherence and compliance	Registration in case report form, exercise log	X	X	
Recurrence and survival	Medical records and Dutch Cancer Registry			
Other				
Sociodemographic data	Self-developed questionnaire	X		
Medical data	Medical records	X		
Adverse events	Reports of patients, physiotherapists, oncology nurses, physicians, medical records	X	X	X

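### Physiotherapist-observed adverse events and weekly weighing exist only in the exercise arm, so all-source event counts by arm are open to detection bias

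*Protocol article*

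**What the plan says.** On adverse events, the Safety section reads: "Adverse events reported by the patient or observed by physiotherapists, oncology nurses or physicians are recorded". The adverse-event row of Table 2 (Study outcomes) gives the source as "Reports of patients, physiotherapists, oncology nurses, physicians, medical records", at baseline, 12 and 24 weeks, for the trial as a whole. The abstract adds that "adherence and safety are monitored throughout the exercise program".

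On weight, the Safety section says: "Body weight is therefore closely monitored by weekly supervised weighing by the physiotherapist". It also sets an alert: "All physiotherapists are instructed to contact the researchers if weight loss exceeds 5% in 1 month, or 10% in total". Such an alert leads to advice being sought from a dietitian or a specialist.

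On who sees a physiotherapist, the Intervention section says that the programme "takes place twice weekly during 12 weeks" and that "All exercise sessions are supervised and guided by a physiotherapist". The Usual care group section describes no physiotherapist, weighing or extra contact. Both arms attend the study centre at baseline and 12 weeks and receive questionnaires by mail at 24 weeks (Study outcomes).

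**The concern.** The list of adverse-event sources reads as one list for the whole trial, but one source on it exists in only one arm. A minor complaint mentioned or noticed at a supervised session can enter the record. The same complaint in a usual care patient enters only if the patient, a nurse, a physician or the medical record brings it up. The same holds for weight: a temporary loss between study visits can be caught by weekly weighing but is easily missed when the only trial weighings are at baseline and 12 weeks.

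Two things are at stake, and they may pull in opposite directions.

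- **Detection.** A table of all recorded events by arm would tend to make exercise look worse than it is. Later analysis cannot recover usual care events that nobody asked about.
- **Extra care.** The consultation that follows a weight alert is a care step described for the exercise arm only. Body weight, malnutrition risk and dietary intake are compared between arms as secondary outcomes, so a difference could partly reflect surveillance and referral rather than training.

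**Working it through.** The plan states no figure on this point, so there is none to reproduce. The check sets the sources side by side and then shows, under labelled assumptions, how much they could matter.

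**Step 1. Sources by arm, up to week 12**

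| Source | Exercise | Usual care |
|---|---|---|
| Patient, nurse, physician and medical-record reports (Safety; Table 2) | yes | yes |
| Study centre visits (Study outcomes) | 2 | 2 |
| Supervised physiotherapist sessions (Intervention) | 2 × 12 = 24 | none described |
| Weekly weighing with alert (Safety) | about 12 | none described |
| Log discussion every 2 weeks (Home-based exercise) | about 12 / 2 = 6 | none described |

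The physiotherapist also documents reasons for missed sessions and sends the forms to the researchers at least every 4 weeks (Adherence). That is a further route by which complaints in the exercise arm can surface.

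**Step 2. What is collected alike.** Deaths, recurrences and new primary tumours come from medical records and the cancer registry (Recurrence and survival). Body weight as an outcome is measured by one procedure at baseline and 12 weeks (Anthropometry; Table 2). None of these depends on the physiotherapist for detection.

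**Step 3. Adverse events, illustration.** Assumptions, not document figures: the same true risk p in both arms, and detection of 0.9 under exercise and s under usual care. The observed risks are 0.9p and s·p, so the apparent risk ratio is 0.9/s whatever p is. The last column uses a two-sided 5% test of two proportions with the planned 75 per arm and p = 0.4.

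| s | Observed risks | Apparent ratio | Chance of a significant excess under exercise |
|---|---|---|---|
| 0.9 | 0.36 vs 0.36 | 1.00 | 2.5% |
| 0.8 | 0.36 vs 0.32 | 1.12 | 7% |
| 0.7 | 0.36 vs 0.28 | 1.29 | 18% |
| 0.5 | 0.36 vs 0.20 | 1.80 | 59% |

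With p from 0.2 to 0.6 and s from 0.8 to 0.5, that chance runs from 5% to 85%.

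**Step 4. Weight loss, illustration.** Assumptions: no average change in weight, measurement error with SD 1.0 to 1.5% of body weight, and random week-to-week steps with SD 0.5 to 0.8%. In a simulation of 200,000 patients per setting, a loss of more than 5% from baseline was seen at some point in 12 weekly weighings in 3.6% to 21.0% of patients. At a single 12-week weighing it was seen in 1.3% to 7.5%. The ratio lies between 0.116/0.0532 = 2.2 and 0.1317/0.0335 = 3.9 across the four settings. More looks find more events even when nothing differs between the arms.

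**The case against.** The strongest reply is that the protocol plans no such comparison. The Statistical analysis section lists mixed models, ANCOVA, Cox regression, effect modifiers and an instrumental variable analysis, but no adverse-event test. Table 2 places adverse events under other data, not among the outcomes. Safety is not a stated aim, and monitoring during training reads as protection of participants. How events are tabulated by source may be settled in the full protocol or the analysis plan. The case report forms are not shown either, and they may already ask both arms the same questions, since patient reports are scheduled for the whole trial.

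Much of this stands. It rules out several stronger statements that a reader might infer:

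- That adverse events are sought weekly. Only the weighing is weekly.
- That adverse events are collected in the exercise arm only. Four of the five sources in Table 2 cover both arms.
- That every between-arm safety comparison is biased. Deaths and recurrences are found in the same way in both arms, and serious events in medical records are less exposed.
- That the bias always runs against exercise. Consultation after an alert could favour it.

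What the reply does not remove is the collection design itself. The article fixes physiotherapists as a source without saying that their reports will be kept apart, and describes no matching enquiry in usual care. Any reader of an all-source table by arm would meet the problem, with or without a formal test.

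**Conclusion.** The point holds in a limited form. All-source counts of non-serious adverse events, and of weight-loss events found by weekly weighing, would tend to be higher under exercise through detection alone. This rests on the text: one adverse-event source and the weekly weighing exist in one arm only. The size does not follow from the text. The ratios of 1.12 to 1.80 merely restate assumed detection rates and show only that modest differences in detection are enough to matter.

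The detection difference does not touch deaths, recurrence or 12-week weight. Weight, malnutrition risk and diet are open to a separate influence, the alert and the consultation that follows, which could favour exercise. The primary outcome analysis does not depend on adverse-event detection. This is a low-cost improvement, not a flaw that threatens the trial's main conclusion.

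**What to change.** - Put the same short questions on adverse events and on dietitian or specialist contacts into the existing 12- and 24-week questionnaires of both arms. If the case report forms already do this, say so.
- Base any between-arm safety table on those answers plus serious events from medical records.
- Report physiotherapist-observed events and weight alerts separately, as a description of the exercise arm.
- State that differences in weight, malnutrition risk and diet are the effect of exercise together with weight surveillance, and use the contact questions to describe how much consultation each arm received.

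The cost is a few questionnaire items and a few sentences in the analysis plan, with no extra staff or visits. The drawback is that minor events would be reported from recall over about 12 weeks. No change to the weight-loss limits or to clinical management is proposed.

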### Sample size

The sample size is based on the primary outcome; improvement in HRQoL from baseline to post-intervention, assessed by the EORTC-QLQ-30. In our previous trial [33, 34], investigating the effects of a 12-week exercise training in cancer survivors, HRQoL in the intervention group improved by 15.1 (SD 17.7) points and the control group by 6.1 (SD 17.1) points; this difference was significant and clinically relevant [35]. We performed a power analysis with PASS, using these results and assuming a power of 80% (alpha = 0.05), which showed that 60 patients are needed in each group to detect an intervention effect. To take into account the correlation between baseline and follow-up in the sample size calculation, Borm et al. developed a method to calculate the sample size, in which the previously calculated number of subjects, should be multiplied by (1-ρ2), plus one extra subject per group [36]. ρ represents the correlation between baseline and follow-up outcomes. In our previous trials we found a correlation of 0.4 between baseline and follow-up HRQoL. By applying the method of Borm et al., we have calculated a sample size of 51 patients per group. We intend to include 75 patients per group taking a drop-out rate of approximately 30% into account (primarily due to early death). This sample size also enables us to detect intervention effects on the secondary outcomes (e.g. physical functioning, VO_2peak_ and fatigue). If drop-out appears to be lower, less patients per group can be included (e.g. in case of a drop-out rate of 10%, 57 patients per group can be included).

### Statistical analysis

Descriptive statistics will be used to describe the study population and study parameters at baseline. Questionnaire scores (e.g. HRQoL and fatigue) will be calculated according to published scoring algorithms. Analyses will be performed according to the intention-to-treat principle. For the primary analysis mixed linear regression models will be used to model the HRQoL outcome measures at 12 and 24 weeks. The models will be adjusted for baseline HRQoL as well as for stratification factors. In these longitudinal analyses, the program accounts for missing data based on the observed data [37]. The same analyses will be performed for the secondary outcome measures. Secondary outcomes, which will only be assessed at baseline and 12 weeks (e.g. VO_2peak_), will be analyzed as between-group differences in outcomes using ANCOVA, adjusted for baseline and stratification factors. Cancer recurrence and survival will be analyzed using a Cox proportional hazards regression model. As an explorative analysis, attendance and compliance, sex, subtype of carcinoma, type of surgery and time since surgery will be examined as potential modifiers of the intervention effects. Furthermore, to adjust for treatment contamination, an instrumental variable analysis will be performed with treatment assignment as instrument and adjustment of the results for adherence [38].

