## Methods

### Design

The primary aim of the PERFECT study is to investigate effects of physical exercise on health-related quality of life in esophageal cancer patients after surgery with curative intent. In addition, we study the effects on fatigue, physical fitness, physical activity, functional wellbeing and symptoms, esophagus-specific QoL, anxiety and depression, diet, sleep quality, anthropometry, work-related factors and blood markers (secondary outcomes). Furthermore, we will explore the effect of physical exercise on disease recurrence and overall survival 5 years after diagnosis. The PERFECT study is designed as a multicenter, randomized controlled trial with two study arms: (1) a group offered a supervised exercise program in addition to usual care and (2) a control group receiving usual care without exercise intervention. We hypothesize that physical exercise leads to higher levels of quality of life, compared with usual care. The PERFECT study protocol has been approved by the Medical Ethics Committee of the University Medical Center Utrecht in December 2014. The study is registered with the Netherlands Trial Registry under NTR5045.

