### Usual care group

Participants in the usual care group receive usual care and are requested to maintain their habitual physical activity pattern.

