#### Physical activity

Physical activity behavior is assessed using the short questionnaire to assess health enhancing physical activity (SQUASH), which includes items on commuting activities, leisure time activities, household activities, and activities at work and school [30].

To assess physical activities (duration/intensity) and duration of sedentary behavior objectively, all participants wear an accelerometer (GT3X+ Tri-Axis Actigraphy Monitor, ActiGraph®) for seven consecutive days at baseline and follow-up measurements. In addition, participants in the intervention group are asked to keep an exercise log during the exercise program. In this exercise log, they document their daily activities.

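### Attendance and compliance are listed as effect modifiers, but they arise after randomisation and are recorded only in the exercise arm, so the explorative analysis is open to confounding by prognosis

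*Protocol article*

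**What the plan says.** The Statistical analysis section states, under an explorative label, that "attendance and compliance, sex, subtype of carcinoma, type of surgery and time since surgery will be examined as potential modifiers of the intervention effects". One list thus mixes two process variables with four baseline characteristics.

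The Adherence section defines the process variables: "Adherence incorporates both attendance at the supervised exercise sessions and compliance (i.e., performing the exercises according to exercise protocol". On recording it says that "the physiotherapist documents presence of each participant at each session in a case report form"; heart rates, durations, weights and repetitions are noted in the same way. The Physical activity section adds that "participants in the intervention group are asked to keep an exercise log during the exercise program".

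The comparator is described under Design as "a control group receiving usual care without exercise intervention". Under Usual care group: "Participants in the usual care group receive usual care and are requested to maintain their habitual physical activity pattern". Recruitment and randomization places allocation after the baseline measurements, hence before any session.

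Straight after the modifier sentence, the Statistical analysis section plans a separate instrumental-variable analysis that uses the randomised assignment as the instrument for adherence.

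**The concern.** To examine an effect modifier is to ask whether the difference between exercise and usual care varies across its levels. For sex or carcinoma subtype, randomisation supplies comparable patients in both arms at every level. For attendance it does not. High attenders are a self-selected part of the exercise arm, and the controls who would have attended equally well cannot be identified.

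The protocol's own account makes selection plausible. The Background describes fatigue, eating difficulties and nausea after surgery. The Sample size section expects about 30% drop-out, mainly through early death. Patients who are deteriorating are likely both to miss sessions and to report poorer quality of life, whether or not exercise helps.

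At stake is how an attendance gradient is interpreted. The Discussion already holds that poor adherence lowers the exercise dose and hence the effect, so a gradient produced by prognosis could be taken as confirmation.

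**Working it through.** **1. Is there a contrast at each level?** Take the usual model: intercept + arm + attendance + arm × attendance. With attendance coded 0 in usual care, the product column equals the attendance column, and the design matrix has rank 3 of 4 (checked numerically). One column must go. What remains is intercept + arm + attendance, where the attendance coefficient is the slope within the exercise arm. It can be estimated, but it is an observational association. If attendance is instead left missing in usual care, the controls leave the model and no arm contrast remains.

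**2. Planning figures (Sample size section).** The mean changes are 15.1 (SD 17.7) and 6.1 (SD 17.1), with 80% power, alpha 0.05 and a baseline/follow-up correlation of 0.4.
- Difference: 15.1 − 6.1 = 9.0 points.
- Pooled SD: √((17.7² + 17.1²)/2) = 17.40.
- Two-sided t-test: 59.7, so 60 per group, as stated (the normal approximation gives 59).
- Baseline adjustment: 60 × (1 − 0.16) + 1 = 51.4; the protocol states 51.
- Drop-out of 30%: 51/0.7 gives 73 and 52/0.7 gives 75; the protocol states 75.

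The stated figures reproduce within rounding. The point does not rest on them; they only set the scale.

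**3. Size of the spurious gap.** Using the protocol's own adjustment factor, the residual SD is 17.40 × √(1 − 0.16) = 15.9. For a median split on a normally distributed attendance score with correlation r to the outcome residual, each half shifts by √(2/π) × r × SD = 0.798 × r × 15.9. The high-minus-low gap is twice that.

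| Assumed r | Shift of each half vs controls | Spurious gap |
|---|---|---|
| 0 | 0 | 0 |
| 0.2 | ±2.5 | 5.1 |
| 0.3 | ±3.8 | 7.6 |
| 0.4 | ±5.1 | 10.2 |

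The values of r are assumptions; the protocol gives none. The SD matters less. If 17.40 is read as the SD of change scores with equal variances at both visits, the residual SD is 17.40/√(2 × 0.6) × √0.84 = 14.6, and the gaps at 0.2 and 0.4 become about 4.7 and 9.3.

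**4. How often would it show?** Simulation: 4,000 trials, 51 per arm, SD 17.40, a constant 9-point effect in everyone (no true modification), median split.

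| Assumed r | Apparent effect, high attenders | Apparent effect, low attenders | Runs with p < 0.05, high vs low |
|---|---|---|---|
| 0 | 9.0 | 8.9 | 5% |
| 0.2 | 11.8 | 6.4 | 20% |
| 0.3 | 13.2 | 4.9 | 41% |
| 0.4 | 14.6 | 3.7 | 63% |

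The gaps are slightly wider than in step 3 because the SD here is 17.40. The percentages do not depend on the SD, since the gap and its standard error scale together.

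**The case against.** **It is only explorative.** This is correct. The primary analysis follows intention to treat, and no sample size or main effect estimate depends on this step. The label limits the consequence but does not remove the confounding.

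**Adherence is already handled by the instrumental-variable analysis.** In part. That analysis rests on randomisation and will sit beside the explorative result, but it is separate and does not repair the modifier analysis.

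**The protocol does not fix a model.** It says only that the variables will be examined. An exercise-arm dose-response analysis, principal stratification, or strata of adherence predicted from baseline would all be possible, and an analysis plan not shown may choose among them. So a reader might infer that the analysis cannot be estimated at all, or that comparing high and low attenders with all controls is the only workable version. The document supports neither: the within-arm slope is estimable, and no alternative is excluded. What stands is the classification, which the text does fix: these two variables are placed with baseline factors as modifiers of the intervention effect.

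**Controls also have activity data, and the Discussion describes contamination as non-compliance of usual care.** The activity questionnaire and the accelerometer do cover both arms. But neither measures attendance or compliance as the Adherence section defines them, and activity during follow-up is itself post-randomisation. Table 2 marks adherence at baseline and 12 weeks, yet its listed sources are the case report form and exercise log of the programme.

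**Conclusion.** The point holds as one of confounding in a single explorative analysis. Attendance and compliance are post-randomisation variables recorded only in the exercise arm, so their association with outcome does not measure modification of a randomised effect. The analysis could suggest a dose-response where none exists, with a spurious gap of about 5 to 10 points for correlations of 0.2 to 0.4 and none at 0. These sizes rest on the assumed correlation, a median split, normality and a residual SD near 15.9.

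Two stronger readings are tempting and not supported. A reader might infer that a dose-response would appear even if exercise did nothing. It could, but in the simulation most trials at correlations of 0.2 and 0.3 showed no significant difference. A reader might also set the gap against the 9-point planning difference. The gap reaches 9 only above a correlation of about 0.35 (9 ÷ (2 × 0.798 × 15.9)), and it compares high with low attenders, whereas the 9 points compare exercise with usual care. Against controls, the shift is at most about 5 points over the range shown.

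**What to change.** In the Statistical analysis section, limit the effect-modifier list to the four baseline factors: sex, carcinoma subtype, surgical approach and time from operation. State that adherence is addressed through the instrumental-variable analysis already planned. Report any association of attendance or compliance with outcome within the exercise arm only, labelled observational. The cost is about one sentence of wording; no data collection, visit or sample size changes.
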